#### Assessment of spasticity and active control zones

Since active elbow extension (active control zone) is limited by the location of the ST in the angular range of the elbow, the ST angle of the elbow flexors (biceps brachii, BB) will be measured. This will allow us to determine the range of angles in which BB cannot be relaxed (spasticity zone) and the range in which reciprocal agonist/antagonist muscle activation is possible (active control zone). The ST angle will be defined using the MSRT, a portable clinical device consisting of a two-channel electromyography (EMG) system (Procomp 5, Thought Technology, Montreal, QC, Canada), an electrogoniometer (servo-type rotational-position potentiometer P2200; Novotechnik U.S. Inc., Southborough, MA, USA) and dedicated software implemented on a laptop computer (Fig. 4). The MSRT has moderate-to-good intra- and inter-evaluator reliability for the measurement of elbow spasticity in post-stroke participants [23].

**Fig. 4 Fig4:**
[figure not shown]
Montreal Stretch Reflex Threshold (MSRT) device. The MSRT is a portable, clinical device consisting of a two-channel electromyography (EMG) system, an electrogoniometer and dedicated software implemented on a laptop computer

BB and triceps brachii (TB) EMG recordings will be obtained with surface electrodes (Ambu® Blue Sensor P, Ballerup, Denmark), from motor points indicated in the Surface ElectroMyoGraphy for the Non-Invasive Assessment of Muscles (SENIAM) guidelines [28]. EMG signals will be band-pass filtered (10–1000 Hz), amplified (×500) and sampled at 2048 samples/s. Seated participants will perform a maximal voluntary contraction of the elbow flexors to adjust EMG gain and initial elbow angle will be specified. Then, 20 stretches will be performed manually by stretching the elbow from flexion (approximately 50^o^) to full extension. Participants will be instructed to relax completely without assisting or resisting the angular displacement. Adequate rest (10 s) will be allowed between stretches to minimize effects of fatigue and muscle thixotropy [29]. Before each stretch, a randomly assigned speed, equally distributed between slow, moderate and fast velocities, will be indicated by an auditory signal from the MSRT to avoid the participant anticipating the upcoming stretch. Each evaluation will last for approximately 20 min. At the end of each stretch, MSRT identifies the angle at which the EMG begins, called the dynamic stretch reflex threshold (DSRT) [23]. At the completion of at least 20 correct stretches, a linear regression line is computed through the DSRTs on the angular velocity/displacement plot from which the correlation coefficient (*r*^2^), slope and x-axis intercept are determined. The x-axis intercept corresponds to the tonic stretch reflex threshold (TSRT) angle. A low TSRT angle corresponds to a high level of spasticity.

#### Arm motor impairment

Voluntary arm motor ability and coordination will be evaluated using the valid and reliable Fugl-Meyer Assessment (FMA) [30–32] that evaluates reflexes, volitional movements and rapid alternating movements. UL scores range from 0 to 66. Sensation (light touch), kinesthesia and passive ROM will be evaluated using FMA scales.

Clinical spasticity in elbow flexors and extensors will be measured with the MAS [18, 19] on six-point ordinal scales (0–1, 1 +, 2–4). The MAS has poor-to-good inter-rater reliability [19, 33, 34].

#### Arm motor function

Arm functional ability will be assessed with the six-item Streamlined Wolf Motor Function Test (S-WMFT) consisting of (1) speed of completion and (2) movement quality scores. Items 1 and 2 are activities involving elbow and shoulder movements and items 3 to 6 are functional tasks. Each item has a maximal time of 120 s and the mean will be reported. In the case of inability to complete a task, a time score of 121 s will be assigned [35]. Functional ability is rated on a six-point scale from 0 to 5 where 0 indicates no attempt to move the affected UL and 5 indicates normal movement. Mean scores will be reported. The S-WMFT has good concurrent (Spearman’s *ρ* = 0.69) and predictive validity (Spearman’s *ρ* = 0.68) with FMA. Responsiveness, as assessed by the standard response mean, was 0.41 [36].

#### Kinematic recording and analysis of reach-to-grasp task

A kinematic assessment of a common daily reach-to-grasp task requiring different amounts of elbow extension will be recorded with a room- and body-calibrated five-sensor wireless electromagnetic tracking system G4 (Polhemus, Colchester, VT, USA; RMS static accuracy 0.20 cm for position and 0.5° for orientation at a distance of 1 m from the transmitter). Each sensor is tracked at a rate of 120 Hz providing six degrees of freedom (three Cartesian and three polar). Sensors will be placed on the index finger metacarpo-phalangeal joint, the proximal third of the dorsal forearm, the mid-lateral surface of the arm, the mid-point of the superior-lateral border of the acromion, and mid-sternum.

Participants will sit in front of a table on a standard chair with no armrests. Arm position will be adjusted so that in the initial position the elbow will be in 30° flexion alongside the body and feet will be supported on the floor. Participants will be instructed to reach to grasp a 6-cm diameter cone “as fast and as precisely as possible,” hold or touch the cone for 2 s, lift the cone or arm towards the chin and then return it to the table. A mid-sagittal reference frame will define four target locations. Targets 1 and 2 will be placed at two thirds and full arm’s length in the mid-sagittal plane, respectively, for which different levels of elbow extension are required. Targets 3 and 4 will be placed at approximately 20 cm to the right and left of Target 2. Arm length will be measured from the medial axillary border to the distal wrist crease with the elbow extended [37]. After several initial practice trials (two trials/target), participants will perform two sets of 40 trials (2 × 10 trials × 4 targets = 80 movements; randomized), in approximately 1 h. Rest between sets and trials will be provided.

Motor behavior will be measured at two levels: endpoint performance and arm movement quality [38]. Endpoint performance includes peak speed; trajectory straightness (index of curvature, IC) [39] where IC > 1.57 describes a semi-circle; and smoothness calculated as the number of velocity peaks in the tangential velocity profile.

For movement quality, joint angles involved in reaching will be measured including shoulder flexion, abduction/adduction and rotation, elbow extension, wrist supination and extension using Euler angles based on standard 3D kinematic reconstruction [40]. Analysis of inter-joint coordination, compensations and pathological synergies will include consideration of trunk and arm plane motion [41].

#### Lesion type, size and location

In a secondary analysis, the relationship between specific lesion type, size and location and treatment outcomes will be assessed.

### Data management

The Oversight Committee will consist of the PIs and one other individual not associated with the trial. The Data Monitoring and Management Committee will be led by an individual who will ensure that all sites upload data from each phase of the trial to a secured, online data repository. Clinical, kinematic and EMG data will be coded for confidentiality. Adverse events due to a-tDCS, training or testing paradigms will be reported to the Ethics Committee at each site by filling out an incident report form. The Ethics Committee will then meet to discuss possible solutions.

### Statistical analyses

Descriptive statistics will be used to highlight main demographic and clinical characteristics of participants. After verification for linearity, normality and homoscedasticity, parametric mixed-model ANOVAs will be used to determine which stimulation and practice modality combinations lead to greater improvements. The mixed-model analysis will include one between-subject factor – group with three levels (personalized training + a-tDCS, non-personalized training + a-tDCS and personalized training + sham-tDCS), and one within-subject factor – time with three levels (Pre, Post and Follow-up). Multiple linear regression analyses on pooled data will identify relationships between primary outcomes and changes in clinical and kinematic measures. If assumptions for parametric tests are not met, non-parametric tests will be substituted. Results will be analyzed based on intention-to-treat principles. Individual participation in other in-patient services will be documented (physiotherapy, occupational therapy, speech therapy, social work, recreation, other) and compared between sites to account for effects of usual-care exposure. Results will be disseminated to individuals, user groups, health care and research professionals at trial completion.

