The sample size is based on preliminary data showing that the mean change in elbow-flexor ST angle was 10° in stroke subjects with spasticity who underwent 2 weeks of transcutaneous electrical nerve stimulation treatment compared to 2° after sham stimulation (unpublished data). Considering an *α* level of 5% and a 95% power (effect size = 2.23) to detect differences using a mixed-design 3 × 3 analysis of variance (ANOVA) (G*Power 3.1.1), the minimal sample size is 13 subjects per group. Sample size was increased to 18 per group to have an equal number of subjects per group per site (six per group, per site). We will recruit 20 subjects per country overall considering a dropout rate of 10–15% for a final cohort of 60 subjects.

Prior to the start of recruitment of participants, standardized procedures will be established to ensure consistency across sites. Intervention therapists will receive training guidelines and evaluators will receive screening and clinical assessment documents. In addition, all team members directly involved in data collection will have face-to-face training on data collection protocols. Quarterly online meetings will be scheduled to maintain adherence to the protocols across sites.

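### The primary 3 × 3 ANOVA uses the Pre value as a time level and not as a covariate: valid, but less precise than a baseline-adjusted analysis of the same data

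*Protocol article*

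**What the plan says.** Under Statistical analyses the article states that "parametric mixed-model ANOVAs will be used to determine which stimulation and practice modality combinations lead to greater improvements". It then fixes the factors: "The mixed-model analysis will include one between-subject factor – group with three levels", and "one within-subject factor – time with three levels (Pre, Post and Follow-up"). No covariate is named, and no term or visit is singled out as the primary test. The same paragraph says: "Results will be analyzed based on intention-to-treat principles".

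Under Participants and recruitment, the trial is sized for the same design: "mixed-design 3 × 3 analysis of variance (ANOVA) (G*Power 3.1.1), the minimal sample size is 13 subjects per group". That number is raised to 18 per group, and 60 people are to be recruited, "considering a dropout rate of 10–15% for a final cohort of 60 subjects".

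The article does not say that a participant with a missed visit is excluded, and it does not say how missed visits are handled.

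**The concern.** Everyone who is randomised has a Pre value of the spatial threshold, and randomisation makes the expected group means equal at Pre. An analysis that uses Pre as a covariate, or holds the group means equal at Pre, exploits both facts. A 3 × 3 ANOVA with Pre as one of three outcome levels uses neither. It estimates a separate Pre mean for each group, and its interaction compares raw changes from Pre. With 17 to 18 completers per group, any avoidable loss of precision counts.

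A second, conditional concern is missing visits. A classical split-plot ANOVA needs all three values from each participant. Someone seen at Pre and Post but not at Follow-up would leave the analysis altogether, including the Post comparison to which that person could contribute. If that is the analysis intended, a complete-case result would be reported as intention-to-treat.

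**Working it through.** **The plan's own figures.** The dropout step reproduces at the lower rate: 3 × 18 = 54, and 54/0.90 = 60. At 15% dropout, 60 × 0.85 = 51 completers, or 17 per group. Completers are therefore 17 to 18 per group, and 60 × 0.10 to 60 × 0.15 = 6 to 9 participants would have a missing visit. The minimum of 13 per group could not be reproduced from an effect size of 2.23. Read as Cohen's d, 2.23 gives about 7 per group by the exact t test at two-sided 5%. That is a separate matter, and nothing below depends on it.

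**Inputs.**
- From the article: 18 per group before the dropout allowance, three groups, α = 5% (taken here as two-sided), planned effect size 2.23.
- Assumed: Pre–Post correlation ρ from 0.3 to 0.8; equal variances at all visits (SD = 1); an effect of 0.8 SD of the outcome between group 1 and one comparator.

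**Variances per participant.**
- Change from Pre: 2(1 − ρ).
- Post adjusted for Pre: 1 − ρ².
- Ratio, adjusted to change: (1 − ρ²)/[2(1 − ρ)] = (1 + ρ)/2.

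**Power of one pairwise contrast.** The noncentrality is 0.8/√(2V/18), where V is the variance above. Error degrees of freedom are pooled over three groups: 51 for change and 50 for adjusted. At ρ = 0.5:
- Change: V = 1.00, noncentrality 0.8/√(2 × 1.00/18) = 2.40, power 65%.
- Adjusted: V = 0.75, noncentrality 0.8/√(2 × 0.75/18) = 2.77, power 78%.

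| ρ (assumed) | V, change | V, adjusted | Ratio | Power, change | Power, adjusted |
|---|---|---|---|---|---|
| 0.3 | 1.40 | 0.91 | 0.65 | 51% | 69% |
| 0.5 | 1.00 | 0.75 | 0.75 | 65% | 78% |
| 0.7 | 0.60 | 0.51 | 0.85 | 86% | 91% |
| 0.8 | 0.40 | 0.36 | 0.90 | 96% | 98% |

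Expressed as sample size, 20 per group analysed as change match 20 × (1 + ρ)/2 per group with adjustment: 13, 15, 17 and 18 for the four values of ρ.

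**Omnibus interaction.** The change contrast is a pairwise stand-in for what the plan's model estimates. With the same 0.8 SD effect in one group at both later visits, 18 per group and compound symmetry, the 4-df group-by-time F test has power 54%, 70%, 92% and 99% at ρ = 0.3, 0.5, 0.7 and 0.8. It tests a different hypothesis and uses both later visits, so it is not a like-for-like comparison with the table.

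**Simulation with dropout.** There were 2,000 runs per scenario, with 20 per group, 10% random dropout (half before Post, half after), and a 0.6 SD effect in one group. The first method is the interaction F among three-visit completers. The second is the baseline-adjusted three-group test at Post in everyone seen at Post.
- ρ = 0.5: 43% for completers' ANOVA, 55% for the adjusted test.
- ρ = 0.7: 67% for completers' ANOVA, 75% for the adjusted test.
- With no true effect, rejection rates at 10% and 15% dropout stayed near 5% for both.
- With an effect of 2.23 SD, power was about 100% for both.

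**The case against.** The strongest reply is that the planned analysis is conventional and valid. The group-by-time interaction compares changes from each participant's own Pre value, so baseline is not ignored, and the type I error holds under random dropout. This stands, and it limits the point to efficiency.

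The 0.8 SD effect and the range of ρ are also this review's assumptions. At the planned 2.23 nothing is lost, and at ρ = 0.8 the gain is two percentage points. This stands as well. Against it, the planned figure comes from unpublished data on electrical nerve stimulation against sham, whereas here every arm trains actively and each comparator shares a component with group 1. A smaller contrast is therefore plausible.

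Two stronger readings are tempting, and the article supports neither:

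- **That dropouts are excluded, contradicting intention-to-treat.** The article nowhere says so. The between- and within-subject wording and the G*Power design point to a classical ANOVA, but the text also speaks of a mixed-model analysis. A likelihood-based mixed model with the same factors would keep partial data, and a design chosen for sizing does not fix the estimation method. Missing-visit handling may also sit in a full protocol or analysis plan that is not shown. The 60 recruits already allow for the loss in numbers, at least at 10% dropout.
- **That the group main effect, diluted by the Pre visit, is the primary test.** The stated aim is to find which combinations improve more, which points to change over time and so to the interaction.

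**Conclusion.** The point holds as an efficiency finding. The article fixes Pre as an outcome level and names no baseline covariate. Under equal variances, adjusting for Pre would cut the variance of a Post contrast by 35% to 10% for ρ from 0.3 to 0.8. For a 0.8 SD effect at 18 per group, that is worth 18 percentage points of pairwise power at ρ = 0.3, about 12 at ρ = 0.5, 5 at ρ = 0.7 and under 2 at ρ = 0.8. The gain is negligible at the planned effect size.

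The conflict with intention-to-treat is conditional. It arises only if the ANOVA is fitted in its classical complete-case form, and it would then affect 6 to 9 of 60 randomised participants at the expected dropout. Severity is should-fix: the planned test is valid, and the improvement is essentially free.

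**What to change.** Replace the 3 × 3 ANOVA for the primary outcomes by a likelihood-based model for repeated measures:

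- outcomes: the Post and Follow-up values;
- fixed effects: group, visit, group × visit, Pre value, Pre value × visit;
- unstructured covariance, REML, and a small-sample correction to the degrees of freedom;
- all randomised participants with at least one post-baseline value, in the assigned arm, using every available visit.

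A constrained longitudinal model that keeps Pre as an outcome with equal group means at Pre serves the same purpose, and it also retains participants with a Pre value only. In either case, take the group contrast at one named post-baseline visit as the primary test, and state that the model uses all available visits. The intention-to-treat statement then rests on an analysis that can deliver it.

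The cost is a change of analysis wording and one or two degrees of freedom. No extra data are needed.

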## Methods

### Aim, design and setting

We hypothesize that in patients with sub-acute spastic hemiparesis after stroke, practice restricted to the active control zone (personalized training) combined with excitatory a-tDCS will improve control over the range of ST regulation in the elbow and improve UL kinematic and clinical performance measures compared to non-personalized training with a-tDCS and personalized training with sham-tDCS. We propose a single-blind, parallel, three-group, randomized controlled trial (RCT; allocation ratio 1:1:1) involving personalized therapeutic intervention to improve control over the range of regulation of STs with the application of excitatory a-tDCS, which, under generally facilitatory conditions (e.g., motivating patients with VR games), may strengthen remaining connections and help restore inter-hemispheric balance. The Standard Protocol Items: Recommendations for Interventional Trials (SPIRIT) flow diagram of study enrollment, interventions and assessments is shown in Fig. 2. In addition, the implementation of such training programs in a low-to-middle-income country will be investigated by including four academic rehabilitation centers in Canada, Israel and India.

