### Participants and recruitment

Sixty people with sub-acute spastic hemiparesis after stroke will be recruited during their hospitalization in rehabilitation centers. In order to achieve adequate participant enrollment, constant chart review of newly admitted patients will be done. Individuals will be included if they have/are: (1) a stroke in the middle cerebral territory, confirmed by magnetic resonance imaging/computed tomography (MRI/CT), and medically stable; (2) aged 25–80 years; (3) in the sub-acute stage of stroke (3 weeks to 6 months post stroke); (4) arm paresis (2–6/7 on the Chedoke-McMaster Stroke Assessment arm score, CMSA [17]) and able to perform at least 30° elbow flexion and extension; (5) elbow flexor and/or extensor spasticity (>1 + out of 4 on the Modified Ashworth Scale, MAS [18, 19]); and (6) able to provide informed consent. Exclusion criteria are: (1) other major neurological or neuromuscular/orthopedic problems or pain interfering with results’ interpretation; (2) medical co-morbidities such as HIV/AIDS, etc.; (3) major cognitive deficits (˂ 20 on the Montreal Cognitive Assessment, MoCA [20]); (4) history of psychiatric disorders, alcohol or drug abuse, seizures, migraines, metal in the cranium, and cochlear and cardiac implants; (5) taking medications (e.g., anti-epileptic and psychoactive drugs) that could affect brain activity [21, 22]. Criteria for discontinuation include participant request or adverse events.

Eligibility will be established by a blinded research coordinator. Participants will provide informed consent and be allocated to one of three treatment groups (*n* = 20 per group) by permuted block randomization, balanced for age (25–50 years/51–80 years) and chronicity (3–12 weeks/13–24 weeks). Participants will receive a training and evaluation schedule, and participation will be monitored by the study coordinator, who will also provide reminders to attend scheduled activities. Travel expenses will be remunerated for follow-up visits.

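### Comparing in-patient service use between sites adjusts no stated estimate and cannot show a usual-care imbalance between the randomised groups

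*Protocol article*

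**What the plan says.** All of the following is in the protocol article.

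- **Usual care (Statistical analyses).** "Individual participation in other in-patient services will be documented", and the record is then to be "compared between sites to account for effects of usual-care exposure". The data are individual; the stated comparison is by site.
- **Main analysis (same section).** "The mixed-model analysis will include one between-subject factor", which is group with three levels. The one within-subject factor is time with three levels. Site and usual care are not among the factors.
- **Second analysis (same section).** "Multiple linear regression analyses on pooled data will identify relationships between primary outcomes and changes in clinical and kinematic measures". No site or usual-care term is named.
- **Setting (Aim, design and setting).** The trial is run by "including four academic rehabilitation centers in Canada, Israel and India".
- **Allocation (Participants and recruitment).** Patients are allocated "by permuted block randomization, balanced for age" and chronicity; site is not named. The sample-size paragraph of the same section nevertheless plans six patients in each group at each site.
- **Blinding (Intervention).** Care providers, outcome evaluators and analysts are blind to group; intervention therapists are not.

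**The concern.** The sentence names a method and its purpose, and the method does not achieve the purpose. A table or test of service use by site is useful description, since care may well differ between three countries, but it changes no estimate unless site or care enters a model. It also looks along the wrong axis for the main question: someone reading the group contrast needs to know whether the three randomised groups received similar other therapy.

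The two analyses are exposed differently. The group contrast has randomisation behind it. The pooled regression does not, and it bears on the question raised in the Background of whether motor recovery goes with recovery of threshold control. If centres differ in care or case mix so that both change scores move together, a link can appear that exists only between centres.

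**Working it through.** The plan gives no figure on this point to reproduce. The check compares the stated model terms with the stated purpose, then sizes the consequence under assumed site differences.

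**Inputs from the protocol.** 60 patients recruited; 18 per group in the sample-size layout, six per group per site. 18 / 6 = 3 sites, so site appears to mean country there, while the setting has four centres.

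**Assumed inputs.** The gap g between the highest and lowest site is 0.5, 1 or 1.5 within-site SD. Three sites have means g x (-0.5, 0, 0.5), so the between-site variance is v = g²/6 = 0.042, 0.167, 0.375.

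**1. Does the comparison enter a model?** The ANOVA has group and time. The regression names primary outcomes and changes in clinical and kinematic measures. Nothing from the site comparison enters either as stated.

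**2. Can a site comparison show a group imbalance?** Suppose one group truly has 1 SD more usual-care hours, in the layout of 3 groups x 3 sites x 6.
- By group: noncentrality = 18 x (4/9 + 1/9 + 1/9) = 12 on 2 and 51 df, giving power of 86%.
- By site: simulation gives a positive result in about 3% of trials.

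With no systematic difference, the largest gap between two of three group means is at least 0.5 SD when the range, divided by 1/√n, is at least 0.5 x √n. That is 2.24 for n = 20 (probability 25%) and 2.12 for n = 18 (29%). An imbalance of that size would go unseen.

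**3. Group contrast without site, groups balanced by site (54 patients).** The expected residual variance is 1 + 54v/51, and interval width grows by its square root.

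| g | √(1 + 54v/51) | Interval too wide by | Type I error |
|---|---|---|---|
| 0.5 | 1.02 | 2% | 4.5% |
| 1 | 1.08 | 8% | 3.4% |
| 1.5 | 1.18 | 18% | 2.2% |

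If groups are not balanced by site, type I error stays at about 5%. Simulated power at a true difference of 0.8 SD (chosen for illustration) is 64%, 59% and 52% without site, against 64 to 65% with it. At the planned effect size of 2.23, power is about 100% in every case.

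**4. Pooled regression, 3 x 20 patients, no true link within sites.** With equal, same-ordered gaps in both change scores, the expected correlation is r = v/(1 + v), and the test statistic centres near r√58/√(1 - r²).

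| g | r | Centre of statistic | False positives, normal approximation | Simulated (40,000 trials) | With site term |
|---|---|---|---|---|---|
| 0.5 | 0.04 | 0.30 | 6% | 6% | 5% |
| 1 | 0.14 | 1.10 | 20% | 20% | 5% |
| 1.5 | 0.27 | 2.16 | 58% | 59% | 5% |

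Sensitivity to the pattern, simulated, for the same three gaps:
- gap halved in one measure: 5%, 9%, 22%;
- two sites swapped in one measure: 5%, 8%, 17%;
- gap in one measure only: 5% throughout;
- four centres of 10, 10, 20 and 20: 6%, 19%, 58%; four of 15: 6%, 15%, 47%.

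With no site gap and a true within-site r of 0.4, adding site lowers power from 90% to 89% (88% with four centres).

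**The case against.** The strongest reply is that a condensed article leaves model detail to a fuller document. The regression's predictors are not listed, and pooled may mean only pooled over groups, so a site covariate is not excluded. This stands in part: the regression figures show what happens if site is omitted, not that it will be. It does not cover the ANOVA, whose factors are listed, or the usual-care sentence, which fixes both comparison and purpose.

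The regression harm also rests on assumed gaps. That is fair. At 0.5 SD the inflation is negligible, and the large values need gaps of 1 SD or more, similarly ordered in both change scores. The analysis is exploratory.

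Tabulating other care by arm is routine, and the individual records already allow it. True, but the article names only the site comparison, so the change is cheap rather than unnecessary.

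Three stronger readings are tempting and not supported:
- **That the group contrast is biased, or its type I error inflated.** Randomisation and blinded care providers keep it unbiased in expectation, and omitting site makes the test at worst conservative.
- **That groups will be unbalanced by site.** Site is missing from the named balancing factors, but the six-per-group-per-site plan suggests allocation may be organised by site; the article does not settle it.
- **That therapy after discharge is missed.** The log is worded for in-patient services and "Travel expenses will be remunerated for follow-up visits", which suggests that some patients are home by then. How many, and when, is not stated, so no finding can rest on it.

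**Conclusion.** The point holds as a mismatch between a stated purpose and a stated method. Comparing service use between sites accounts for usual care in neither stated analysis and cannot show an imbalance between the randomised groups.

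For the group contrast the consequence is modest: some lost precision, and a chance imbalance in other therapy that nobody would see. For the pooled regression it ranges from nothing to serious, depending on whether both change scores differ across sites in a similar order, which the protocol gives no data to judge. The 59% is the far end of an assumed range, not a forecast. The change is worth making because it is cheap and the protocol itself anticipates site differences in care.

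**What to change.** 1. Reword the usual-care sentence so that individually recorded service use is tabulated by randomised group within site. This keeps the site description and adds the missing axis.
2. Add site and site x time to the mixed-model ANOVA, and state whether site means country (three levels) or centre (four).
3. Include site in the pooled regression.
4. Do not adjust the group contrast for therapy hours, which arise after randomisation.

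**Cost.** In the ANOVA, site plus site x time uses 2 + 2 x 2 = 6 degrees of freedom with three sites, or 3 + 3 x 2 = 9 with four centres. The regression loses about 1 to 2 points of power, and a site term sets aside any true link visible only between sites. No new in-patient data are needed, and the intention-to-treat set is unchanged.

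**Optional.** Ask about out-patient services at Follow-up, and report a sensitivity regression adding individual hours and group. Site alone does not remove confounding within sites: if hours correlate 0.2, 0.3 or 0.4 with both measures, false positives with site are 6%, 10% and 22%, and adding hours returns them to 5%. Label it as a sensitivity analysis, because hours may respond to recovery and group may carry treatment-driven change in both measures.
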